### Sample Size Planning

At T0, no participant will meet the WHO-recommended PA level according to the inclusion criteria. We assume that 10% of participants in the control group will meet the WHO-recommended PA level at T2 as there are minimum interventions. A target sample size of 97 per group (194 in total) would allow us to detect a between-group difference of 15% in the prevalence of meeting the WHO-recommended PA level at T2 (25% versus 10%; power=0.80, α=.05, PASS version 11.0 [NCSS Statistical Software]). We conservatively estimate the dropout rate to be 30% at T2. Thus, 139 eligible participants per group (278 in total) are required.

### Ethical Considerations

Ethics approval was obtained from the Survey and Behavioural Research Ethics Committee of the Chinese University of Hong Kong (approval number SBRE-22-0257) and the Joint Chinese University of Hong Kong – New Territories East Cluster Clinical Research Ethics Committee (approval number 2022.610-T). All participants will fill out an electronic consent form through a link sent over WhatsApp to confirm their informed consent. The electronic consent forms and participants’ contact information will be kept separately from the questionnaires in a locked cabinet in the office of the principal investigator. Participants’ names and contact information will not appear on the questionnaire or in the dataset. A unique study ID will be assigned to each participant throughout the study. The dataset will be protected by a password on the computer of the principal investigator. All data will be kept for 5 years after conclusion of the project. The data will be disposed of or deleted securely and confidentially once the retention period has expired.

A supermarket coupon worth HK $50 (US $6.37) will be mailed to an address provided by the participants upon completion of the surveys at T0, T1, and T2. A supermarket coupon worth HK $150 (US $19.11) will be given to the participants in the same manner after they finish wearing and return the accelerometers at T0, T1, and T2.

### Development and Maintenance of the Chatbot

A chatbot will be developed and maintained on the WhatsApp platform due to its wide popularity among local older adults and a user-friendly interface. The architecture of the chatbot system is shown in Figure 2. Users send information to the WhatsApp instant messaging server, which then delivers the message to the chatbot. The chatbot system processes and sends a message back to WhatsApp, where users can view the information. The knowledge graph, which links participants’ input with the chatbot’s responses, will be prepared by focus groups of 30 older adults and interviews with experts in sports medicine. The knowledge graph will evolve over time with an increasing number of human-chatbot interactions. The chatbot will use a mixture of techniques so that the human-chatbot interactions are not merely rule based, and the chatbot will also learn from the evolving knowledge graph through machine learning. We will pilot the chatbot among another 30 older adults to improve its accuracy of human-chatbot interactions. These measures will allow the chatbot to have adequate accuracy and consistency in delivering interventions according to the protocol and prevent the chatbot becoming repetitive and off-topic after extensive usage. The same professional team will maintain the health status of the chatbot during the intervention period. A monthly review of the chatbot’s performance will be conducted.

**Figure 2 figure2:**
[figure not shown]
Architecture of the chatbot system.

### Baseline Survey and Randomization

Participants will be interviewed over the phone to record their background characteristics and potential confounders at baseline. Their PA in the first week after the baseline survey will be measured using an accelerometer. At the end of the baseline survey, the interviewers will help participants install WhatsApp on their smartphones, if needed. Computer-generated random allocation codes will be produced and sealed in opaque envelopes by a research staff member, without involvement in recruitment or the baseline survey. One envelope will be drawn and opened by the interviewer, who will then inform each participant about their assigned group. Block randomization with a block size of 8 will be used. Our project staff will connect participants’ WhatsApp with the chatbot, and the chatbot will automatically run a training module guiding users in an older adult–friendly way when participants access it for the first time.

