### Objectives

The proposed RCT will compare the efficacy of an SOC- versus a non-SOC-tailored intervention in increasing the prevalence of meeting WHO-recommended PA levels 6 months after completion of the intervention among inactive community-dwelling individuals aged ≥65 years. Given the strengths of chatbots in health promotion, both the SOC- and non-SOC-tailored interventions will be delivered by a chatbot with natural language processing (NLP) functions. The PA levels will be measured using the validated Chinese version of the International Physical Activity Questionnaire Short Form (IPAQ-SF) and accelerometers.

The secondary objectives of this RCT are to compare the following outcomes 6 months after completion of the intervention between the intervention and control groups: (1) minutes of MPVA, low-intensity PA, and sedentary time in the past week measured using both the IPAQ-SF and accelerometers; (2) step counts in the past week measured using accelerometers; (3) SOC levels, perceived pros, perceived cons, and perceived self-efficacy related to PA; (4) compliance to the web-based interventions; and (5) cognitive status.

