## Methods

### Study Design

This is a partially blinded (outcome assessors and data analysts) and parallel-group RCT to be conducted in Hong Kong, China. Inactive community-dwelling people aged 65 years or more will be randomized evenly (1:1) into either an intervention group or a control group. In the intervention group, the chatbot will measure participants’ SOC related to PA and deliver web-based interventions tailored to their current SOC every week for 12 weeks. In the control group, the chatbot will not measure participants’ SOC but will deliver a standard and non-SOC-tailored web-based intervention every week for 12 weeks. Participants will be interviewed at baseline (T0), after completion of the intervention (T1), and 6 months after T1 (T2). The study was registered at ClinicalTrials (NCT06641492). The study flowchart diagram is shown in Figure 1. We will report this trial in accordance with the CONSORT-EHEALTH (Consolidated Standards of Reporting Trials of Electronic and Mobile Health Applications and Online Telehealth) checklist (Multimedia Appendix 1) [31] and the SPIRIT (Standard Protocol Items: Recommendations for Interventional Trials) checklist (Multimedia Appendix 2).

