### Participants and Recruitment

Inclusion criteria are as follows:

Age 65 years or more.Having a Hong Kong identity card.Chinese speaking.Not meeting the WHO-recommended level of MVPA, defined as <150 minutes of moderate-intensity aerobic PA in the past week. The interviewers will assess participants using the validated Chinese version of the IPAQ-SF.Willing to be followed over the phone at T1 and T2.Owning a smartphone.Able to send and read text/voice messages via smartphones.Willing to wear an accelerometer for a week at T0, T1, and T2.

Exclusion criteria include the following:

Blindness or deafnessDiagnosis of major psychiatric diseases (schizophrenia or bipolar disorders) or dementiaScore≥1 in the Chinese version of the Physical Activity Readiness Questionnaire (PAR-Q)Score≤16 in the validated telephone version of the Cantonese Mini-mental State Examination (T-CMMSE) [32]

Participants will be recruited through random telephone calls. Telephone numbers will be selected from up-to-date Hong Kong telephone directories. Trained interviewers will call potential participants over the phone. If there is more than one person in the household who is aged ≥65 years, the one whose birthday is closest to the interview date will be invited for the study to avoid contamination and introduction of extra confounding factors. Interviewers will brief prospective participants about the study and screen their eligibility.

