#### Secondary Outcomes

The following secondary outcomes will be measured at T0, T1, and T2:

Step counts and minutes of MVPA, light PA, and sedentary time in the past week measured using accelerometers.Compliance with the web-based interventions, including the number of intervention sessions started and completed, as documented by the chatbot.The SOC related to the PA measured using a validated multiple-choice question [34]. The measurement and definition of the SOC will be the same as those used by the chatbot. In addition, we will extract the SOC measured by the chatbot at the beginning of each intervention session in the intervention group from the chat history.Perceived pros and cons related to PA will be measured using the validated questionnaire on decisional balance developed by Nigg et al [35], which consists of 10 questions with 2 scales (pros and cons).Perceived self-efficacy of PA will be measured using a validated 6-item scale developed by Marcus et al [34].Cognitive status will be measured using cognitive tasks, including the sustained attention test [36], working memory [37], inhibitory control [38], and cognitive flexibility [39].

The outcome assessors and data analysts will be blinded to the treatment allocation. Participants will be reminded not to disclose the intervention they receive to assessors.

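### Interviewers who screen participants also open the envelope and announce the group under one block size of 8, which exposes the self-reported outcomes, and to a lesser degree later allocations, to avoidable bias

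*Protocol article*

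**What the plan says.** All references are to the Protocol article.

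- **Enrolment** (Participants and Recruitment): "Interviewers will brief prospective participants about the study and screen their eligibility". For the inactivity criterion: "The interviewers will assess participants using the validated Chinese version of the IPAQ-SF".
- **Preparing the allocation** (Baseline Survey and Randomization): "Computer-generated random allocation codes will be produced and sealed in opaque envelopes by a research staff member, without involvement in recruitment or the baseline survey".
- **Opening and announcing it** (same section): "One envelope will be drawn and opened by the interviewer, who will then inform each participant about their assigned group".
- **Blocking** (same section): "Block randomization with a block size of 8 will be used".
- **Blinding** (Study Design): "This is a partially blinded (outcome assessors and data analysts) and parallel-group RCT". Secondary Outcomes adds: "The outcome assessors and data analysts will be blinded to the treatment allocation". It also says that participants will be asked not to reveal their intervention to assessors.
- **Comparability of the arms** (Objectives): "both the SOC- and non-SOC-tailored interventions will be delivered by a chatbot". The sections on the two groups show that both arms have weekly sessions for 12 weeks, IPAQ-SF feedback, video or information content, the same list of common problems and the same knowledge graph. Only the intervention arm gets the stage-of-change question and stage-specific content.
- **Outcome measurement** (Primary Outcome): physical activity comes from the IPAQ-SF and from a waist-worn accelerometer. Randomization is placed after the baseline telephone survey and after the invitation to collect the accelerometer.

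**The concern.** Two separate exposures follow from one procedural choice.

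**Participant knowledge.** Someone told which group they are in may answer differently. The IPAQ-SF, the stage-of-change item, the pros and cons scales and the self-efficacy scale all rest on self-report. If people who know they have the programme under test report more favourably, the bias favours the intervention. The protocol gives no reason for the disclosure and does not list it under Limitations. Because participants know their group, they can also reveal it at T1 and T2, so the blinding of assessors depends partly on their discretion.

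**Recruiter knowledge.** A person who screens, sees each allocation and knows that every block holds four of each arm can sometimes work out what comes next. That matters if it can influence who is enrolled.

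**Working it through.** **1. The plan's own figure.** The plan states no figure for predictability. Its sample size is used in step 4, so it is reproduced here. With 25% versus 10%, two-sided α = .05 and power 0.80, the unpooled formula is

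n = [p1(1−p1) + p2(1−p2)] × (z for α/2 + z for power)² / (p1−p2)²,

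with p1(1−p1) + p2(1−p2) = 0.1875 + 0.09. This gives 96.8, so 97 per group. Allowing for 30% dropout, 97/0.70 = 138.6, so 139 per group. Both match the plan, and nothing in this point changes them.

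**2. Predictability within a 1:1 block of 8.** There are 70 possible sequences (8 choose 4). All were enumerated for an observer who sees each earlier allocation and knows the block size.

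- An allocation is fully determined once one arm has used its four places. The mean number determined is 1.6 per block, which agrees with the closed form 2m/(m+1) for m = 4: 8/5 = 1.6. As a share, 1.6/8 = 20%.
- Guessing the arm with more places left is right 5.33 times per block. The closed form agrees: 4 + 128/70 − 0.5 = 5.33. As a share, 5.33/8 = 66.6%, against 50% by chance.

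For comparison, known fixed blocks of 4 and 6 give 33% and 25% determined, and 70.8% and 68.3% guessable. Smaller blocks are no protection in themselves. The protection comes from recruiters not seeing allocations and not knowing the sizes.

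**3. How far the timing lowers these ceilings.** Results reports 185 randomized between November 2024 and the end of February 2025. Counting from 1 November, that is 120 days or 17.1 weeks, and 185/17.1 = 10.8 per week (more if recruitment began later in the month). Screening is by telephone, and randomization comes later; the exact gap is not stated. If it were about a week (an assumption), roughly 11 people would be screened but not yet allocated at any time, which is more than one block of 8. An interviewer then screening someone could not tell which envelope that person would reach. If the gap is short, the figures move back towards 20% and 67%.

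**4. What differential reporting could do (illustration).** The documents give no size for this bias, so it is assumed. Suppose there is no true effect, 10% meet the level in each arm by IPAQ-SF, and 97 per arm are analysed. Over-reporting then classes an extra x in the intervention arm as meeting the level. The chance of a significant two-sided result from a pooled z test is

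Φ[(x − 1.96·se0)/se1] + Φ[(−x − 1.96·se0)/se1].

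For x = 5 points: pooled p = 0.125, se0 = √(2 × 0.125 × 0.875/97) = 0.0475, and se1 = √((0.15 × 0.85 + 0.10 × 0.90)/97) = 0.0474. The result is 18%.

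| Extra classed as meeting the level | Chance of a false positive |
|---|---|
| 0 points | about 5% |
| 2 points | about 7% |
| 3 points | about 10% |
| 5 points | about 18% |
| 10 points | about 50% |

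This applies to a result based on the IPAQ-SF. It does not apply to accelerometer data.

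**The case against.** Much can be said for the plan as written.

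- **Concealment.** The envelopes are opaque, sealed and prepared by someone outside recruitment, so the current allocation is protected. Contacts come from random calls with a birthday rule within the household, and much of eligibility is scored, so there is limited room to act on a guess. Nothing says that interviewers know the block size or see every allocation. This stands, and it is why the 20% and 67% are ceilings only.
- **Assessor blinding.** A reader might infer that the interviewers who open envelopes also carry out the T1 and T2 interviews, so that assessor blinding is already broken. The documents do not say so. They state that assessors are blinded, and who conducts follow-up is a detail an article may leave to the full protocol.
- **Contradiction.** A reader might also see a conflict with the blinding claim. There is none: the trial calls itself partially blinded and never claims that participants are masked.
- **Objective measurement.** The primary outcome is also measured by accelerometer, as are step counts and the activity and sedentary minutes. Over-reporting cannot alter device data. This stands and confines the reporting concern to the IPAQ-SF version and the self-reported scales. The protocol does not say which instrument decides the primary outcome, so the concern does not disappear.
- **Group labels.** The words used to announce the group are not given, and intervention participants may notice the weekly stage question. Still, someone who never sees the other version has little basis for knowing which one is under test unless told.
- **Late remedy.** 185 of 278 had already been randomized at the reported date. This limits the benefit but does not remove it.

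**Conclusion.** The point holds as an avoidable design weakness with a cheap remedy. Because the two programmes are so alike, telling participants their group exposes self-reported outcomes to differential reporting and makes assessor blinding rest partly on participant discretion, with no stated gain. The size of that reporting bias cannot be derived from the documents. Under the assumptions shown, 3 to 5 points of differential over-reporting would double to more than triple the false-positive rate of an IPAQ-SF result.

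The allocation part is weaker. At most 20% of allocations are determined and 67% guessable. That requires one interviewer who knows the block size and sees the whole sequence, with allocation soon after screening. The described order of events makes the true figures lower, by an amount the article does not let one compute. It would be wrong to conclude that the accelerometer results are open to over-reporting or that assessors are in fact unblinded.

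**What to change.** **For participants not yet randomized** (278 − 185 = 93 at the reported date):

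1. Have the project staff who already connect each participant's WhatsApp to the chatbot open the next sequentially numbered envelope and assign the version. Interviewers do not see it.
2. Tell participants only that they will receive one of two chatbot physical activity programmes.
3. Use block sizes that vary at random (for example 4, 6 and 8) and are not disclosed to recruiters. Steps 1 and 3 belong together, because small blocks seen by recruiters would be more predictable.

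**For participants already told their group:** have the T1 and T2 interviews done by staff who did not open that participant's envelope. If recruitment has closed by the time this is read, this step and the reporting below are what remain.

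**Cost.** This needs a change of procedure and of the briefing and consent wording, but no extra staff and no change in sample size. The downside is that about two-thirds of participants (185/278 = 67%) are already unmasked, so masking will be mixed over calendar time. The trial report should say so and give the date of the change.

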### The Intervention Group

The interventions will start after participants complete baseline PA measurements with the accelerometer. The chatbot will deliver interventions cocreated by researchers and older adults based on the behavioral change strategies recommended by the SOC-tailored intervention to address the determinants of PA among older adults identified by previous studies. Twelve weekly sessions of the SOC-tailored intervention will be delivered by the chatbot within 3 months through WhatsApp. In previous studies, 3 months was the most commonly selected intervention duration for web-based interventions promoting PA among older adults [2]. Moreover, 1 study suggested that some older adults would lose interest if the duration of web-based interventions was longer than 3 months [20]. Multimedia Appendix 3 shows the workflow of the intervention group. The intervention steps are described next:

Step 1: Initiate the intervention. The chatbot will greet participants and state its function and topics to be covered.Step 2: Measure the PA level. The chatbot will ask participants to fill out the Chinese version of the IPAQ-SF. The chatbot will automatically calculate their MVPA level and provide feedback based on that level.Step 3: Identify the SOC. The chatbot will ask participants a validated multiple-choice question [20] that has been widely used to identify the SOC related to PA: Which sentence best describes your current PA situation? The response categories are “I participate in PA for less than 150 minutes per week and do not intend to increase that time in the next 6 months” (precontemplation stage), “I participate in PA for less than 150 minutes per week and intend to increase that time in the next 6 months” (contemplation stage), “I participate in PA for less than 150 minutes per week and intend to increase that time in 1 month” (preparation stage), ”I participate in PA for at least 150 minutes per week, but I have only begun to do so in the past 6 months” (action stage), and “I participate in PA for at least 150 minutes per week and have been doing so for more than 6 months” (maintenance stage).Step 4: Deliver interventions tailored to participants’ current SOC levels. The intervention will address known determinants of PA among older adults identified in a systematic review and a local study [9,10]. Barriers to PA among older adults include a lack of knowledge, skills, capacities, or support from peers or family members related to PA, the perception that PA would cause pain or injury, difficulties in accessing sports facilities, and concerns about bad weather. The facilitators include perceived benefits of PA on physical and mental health, perceived self-efficacy to perform PA, and suggestions from health professionals.

#### The Precontemplation Stage

Participants in the precontemplation stage will watch a web-based video in which a sport scientist explains the definition of PA, emphasizes adequate levels of MVPA important for physical and mental health, and introduces levels of MVPA recommended by WHO for older adults. This content seeks to increase participants’ awareness of the importance of adequate MVPA.

#### The Contemplation Stage

Participants in the contemplation stage will watch a different web-based video. The same sports scientist will talk about the benefits of adequate MVPA for older adults (eg, reducing dependence-inducing diseases, such as cardiovascular diseases and cancers, and improving cognitive function, frailty syndrome, performance of physical functions, and mental health), address physical and environmental barriers to PA by introducing feasible options of PA suitable for older adults that can be performed at home or in the community, and give recommendations and encourage older adults to make a plan for PA. In addition, several older adults who perform MVPA regularly will share their positive experiences during PA (eg, better physical functions, a stronger immune system, and a positive psychological status) and how they overcame physical and environmental barriers of PA. This content aims to increase self-efficacy and perceived pros and reduce perceived costs of PA.

#### The Preparation Stage

The chatbot will provide a dropdown list of easy and enjoyable PA options that are suitable for older adults, which will be identified by focus groups of older adults and suggestions of the sports scientist, in the preparation stage. These options will include brisk walking, aerobics, stretching, strength/muscle training, Tai Chi, and 8-section brocade exercise. Participants will be invited to select one or more options from the list. The chatbot will retrieve a predesigned demonstration video related to each option and send it to participants. This content seeks to assist participants in developing and implementing an action plan, as well as increase their perceived self-efficacy related to PA.

